#### Randomisation

The Guardian® system will prompt the health professional providing care to consider whether the woman is eligible for the INFANT trial, when EFM has been used for more than 5 min. Intermittent use of EFM for periods of up to 5 min duration may be used for intermittent monitoring, but when used for longer periods of time this will often indicate that a decision has been made to initiate continuous EFM, in which case the women may be eligible to participate in the trial. If the health care professional indicates that the women is not yet eligible because an active decision has not been made to initiate continuous EFM, then the Guardian® system will prompt the health care professional again, if the CTG continues to be recorded for longer than 5 min in this or any subsequent episode of monitoring.

When the health care professional indicates that a woman is eligible to participate, the Guardian® system will clarify that the necessary eligibility criteria for trial entry have been met, i.e. that the health professional gives the required answers to a number of questions posed by the Guardian® system and then the Guardian® system will randomly allocate the women in the ratio 1:1 to either “CTG with no decision-support” or “CTG with decision-support”. The allocations will be computer generated in Stata software (release 10) using stratified block randomisation employing variable block sizes to balance between the two trial arms by whether the pregnancy is a singleton or twins, and within each participating centre. The procedures for randomisation will be fully documented, reviewed and signed off prior to the start of the trial and monitored by the co-ordinating centre during the trial.

As all de-identified information collected by the Guardian® system within the participating centre can be accessed centrally, the trial co-ordinating centre and the participating centres will be able to monitor the performance of centres in terms of the number of women the Guardian system considers eligible who are recruited to the trial to ensure that the necessary systems within the centre are optimised to maximise recruitment.

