#### Effect size

The effect size which can be detected with 46,000 women (23,000 in each group), assuming a 5 % level of significance and 90 % power, is a 50 % reduction in poor neonatal outcome rate from 3 to 1.5 per 1000. We have approximated the number of women recruited with the number of infants born, even though women with a twin pregnancy are eligible to join the trial. Approximately 1 in 80 pregnancies are twin pregnancies, however, a proportion of these births will occur before 35 weeks’ gestation and a large proportion of the term births will be by elective caesarean section. We therefore estimate that fewer than 1 % of all births in the study will be twins. In a study of 164 preterm infants [29], the mean (SD) PARCA-R composite score at 2 years was 80 (SD 33) and the mean Mental Development Index (Bayley Scales of Infant Development II) was approximately half a standard deviation below the standardised mean of 100. If we assume that a normal group of term infants would have a PARCA-R composite score half a standard deviation above this sample of preterm infants, then we can estimate a mean (SD) 2 year score of 96 (SD33). Based on this estimate, a follow up sample of size 7000 (3500 per arm) in the INFANT study would have over 90 % power to detect a difference of 3 points in the PARCA-R component score with a two-sided 5 % significance level. The incidence of severe metabolic acidosis (cord-artery pH <7.05) is 10 per 1000 [36–39]. Our proposed sample size will therefore enable us to detect a 28 % relative risk reduction in incidence with over 80 % power in those babies who have their cord artery pH measured.

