#### Primary analysis

The primary analysis will be a comparison of women and babies allocated to “CTG with no decision support” with “CTG with decision support”. Participants will be analysed in the groups into which they were randomly allocated, regardless of allocation received. All women and babies with available data will be included, except for protocol violations and women randomised in error who did not give consent or who were under 16 years of age. The number (percentage) of babies with the composite primary outcome will be presented for each group, and the risk ratio plus 95 % confidence interval (CI) will be calculated. Risk ratios will be estimated using generalised estimating equations (GEE), or a similar method, adjusting for the stratification factors used in the randomisation (centre and singleton/twin pregnancy). This method of analysis will account for the correlation in outcomes between twins and siblings delivered in a subsequent pregnancy during the trial period. A log binomial model will be used in the first instance, but if convergence is not achieved then a log Poisson model will be used with a robust variance estimator [40]. The mean (SD) PARCA-R Composite score will be presented for each group, and the mean difference between groups plus 95 % CI will be calculated and compared using GEE (Gaussian model with identity link). For secondary outcomes including the components of the primary outcome, a 1 % level of statistical significance will be employed. Both adjusted and unadjusted estimates will be presented for all outcomes, but the primary inference will be based on the adjusted analysis.

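### The power stated for metabolic acidosis (28 % reduction, over 80 %) is not available at the 1 % level set for secondary outcomes: there it is at most about 75 %, even with complete cord pH data

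*Protocol article*

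**What the plan says.** The *Effect size* section of the protocol article gives the trial size ("23,000 in each group") and then adds a power statement for acidosis. It states: "The incidence of severe metabolic acidosis (cord-artery pH <7.05) is 10 per 1000". It continues: "Our proposed sample size will therefore enable us to detect a 28" % "relative risk reduction in incidence with over 80" % power, limited to the comparison "in those babies who have their cord artery pH measured". No significance level is attached to this sentence. The two other calculations in the section both use 5 %: the primary composite at a 5 % level, and PARCA-R, where the wording is "component score with a two-sided 5" % level.

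The *Secondary outcomes* section lists metabolic acidosis, defined there as cord artery pH <7.05 together with a base deficit of at least 12 mmol/l.

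The *Primary analysis* section fixes the test level: "For secondary outcomes including the components of the primary outcome, a 1" % level of significance is to be used. It makes no exception for acidosis.

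**The concern.** A power figure has meaning only at the significance level at which the result will be judged. Here the power sentence and the decision rule are both stated in the current text, in different sections, and they do not fit together. A reader of *Effect size* would naturally carry over the 5 % used for the neighbouring calculations. A reader of *Primary analysis* learns that acidosis will be judged at 1 %.

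Acidosis is the only listed secondary outcome for which the article states a power. If its result were not significant at 1 %, someone relying on the stated power could put the chance of missing a true 28 % reduction below 20 %. Under the plan's own rule it is at least about 25 %, and more if cord gases are incomplete.

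**Working it through.** **Inputs**
- Control incidence p1 = 0.010 (*Effect size*).
- 28 % relative reduction, so p2 = 0.010 × 0.72 = 0.0072 (*Effect size*).
- 23,000 per arm (*Effect size*), allocated 1:1 (*Randomisation*: "randomly allocate the women in the ratio 1:1").
- Alpha: 5 % elsewhere in *Effect size*; 1 % for secondary outcomes in *Primary analysis*.
- Share of babies with cord pH measured: not given, so shown as a range.
- Assumption: two-sided testing. This is stated for PARCA-R and not restated for acidosis.

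**Formulas** (two proportions, variance pooled under the null)
- Mean proportion p̄ = (0.010 + 0.0072)/2 = 0.0086
- s0 = √[2p̄(1 − p̄)] = 0.1306; s1 = √[p1(1 − p1) + p2(1 − p2)] = 0.1306
- n per arm = [z(1−α/2)·s0 + z(power)·s1]² / (p1 − p2)²
- Power = Φ{[(p1 − p2)√n − z(1−α/2)·s0] / s1}

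**Step 1: reproduce the stated figure at 5 %**
- 80 % power: n = [(1.960 + 0.842) × 0.1306]² / 0.0028² ≈ 17,071 per arm, or about 34,140 in total. 17,071/23,000 = 74 %.
- All 23,000 per arm measured: 0.0028 × √23,000 / 0.1306 = 3.25; Φ(3.25 − 1.96) = 90.2 %.

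So at two-sided 5 % the claim of over 80 % is correct provided at least about 74 % of babies are measured.

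**Step 2: apply the 1 % level**
- All 23,000 per arm measured: Φ(3.25 − 2.576) = Φ(0.676) ≈ 75.1 %.
- 80 % power: n = [(2.576 + 0.842) × 0.1306]² / 0.0028² ≈ 25,401 per arm, or about 50,800 in total. This exceeds 46,000. It also exceeds what twins could add: with up to 1 % more babies there would be about 23,230 per arm.

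**Step 3: separate the effect of alpha from that of missing cord gases** (power for 10 v 7.2 per 1000)

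| Share measured | Per arm | Power at 5 % | Power at 1 % |
|---|---|---|---|
| 100 % | 23,000 | 90.2 % | 75.1 % |
| 90 % | 20,700 | 87.0 % | 69.5 % |
| 80 % | 18,400 | 82.9 % | 63.0 % |
| 75 % | 17,250 | 80.4 % | 59.5 % |
| 60 % | 13,800 | 71.2 % | 47.7 % |
| 50 % | 11,500 | 63.3 % | 39.1 % |

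Reading across a row gives the effect of the stricter level; reading down a column gives the effect of incomplete measurement.

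**Step 4: reduction detectable with 80 % power at 1 %**
- All measured: 29.3 %.
- Three quarters measured: 33.4 %.

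**Step 5: robustness.** With all babies measured, power at two-sided 1 % lies between 73.4 % and 75.4 % across unpooled, log risk ratio, arcsine and continuity-corrected versions and a simulation of the pooled test.

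**The case against.** **The sentence names no alpha, so it contradicts nothing outright.** This stands in part. A reader might infer that the claim works only at 5 %, or that its arithmetic is wrong. The article supports neither. With every baby measured, power exceeds 80 % at any two-sided level above about 1.6 %, and at 5 % the figure reproduces. That 5 % was used is an inference from the rest of the section, and the 74 % share is solved back from the claim; it is not a figure in the article. What remains is that the one level the article sets for this outcome, 1 %, lies below the range where the claim holds.

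**The loss due to alpha is small.** Measured against the claim, with full measurement it is 75 % instead of 80 %, or a detectable reduction of 29.3 % instead of 28 %. This is fair. A reader might also infer from the lowest figures that the 1 % rule cuts power to 48 % or 39 %. That would be wrong: at 60 % and 50 % measured, power is already only 71 % and 63 % at the 5 % level, and the article does not give the share measured. It does limit the claim to measured babies, and *Data collection* says that not every field is collected at every centre, so full measurement is a ceiling and not an expectation.

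**A one-sided 1 % test would give 82 %.** Nothing in the article supports one-sided testing, and that variant would still need about 95 % of babies measured (21,828 of 23,000 per arm).

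**No decision depends on the figure.** True. The trial size rests on the primary composite, no stopping rule uses the acidosis power, and estimates will be presented for all outcomes. This limits the consequence to how a null acidosis result is read; it does not make the stated power correct.

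**Conclusion.** The point holds as an inconsistency between a stated power and the stated test level. Under the article's own rule for secondary outcomes, the trial does not have over 80 % power for a 28 % reduction from 10 per 1000. It has at most about 75 %, and about 60 % if three quarters of babies are measured, against 80 % at the 5 % level for that same share. About 50,800 measured babies would be needed for 80 %.

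This rests on two-sided testing and on taking 10 per 1000 as given. That incidence is tied to pH <7.05 alone, while the listed outcome also requires a base deficit of at least 12 mmol/l. Its incidence on that basis can only be equal or lower, so for the same relative reduction the 1 % figures are an upper bound on power.

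A reader might take this as a sign that the trial as a whole is too small. It is not: the primary sample size is a separate calculation and is unaffected.

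**What to change.** In *Effect size*:

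1. State the significance level for the acidosis sentence.
2. Delete the claim of over 80 % power for a 28 % reduction and give the figure at the level in *Primary analysis*. For example: at the two-sided 1 % level, the trial has 80 % power for a 29 % reduction from 10 per 1000 if all babies have a cord artery pH, and for about a 33 % reduction if three quarters do.
3. Say that 10 per 1000 refers to cord artery pH <7.05 alone, so that for the secondary outcome as defined, which adds the base deficit criterion, the stated power is an upper bound.

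The cost is one or two sentences and a less favourable figure. No extra participants or data are needed, and neither the analysis nor the primary sample size changes.

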#### Assumptions

Variations in some of the assumptions of incidence will produce marked variations in the required sample size as the overall incidence is so low. For example, Table 2 illustrates the impact on the required sample size assuming a 5 % level of significance and 90 % power for the same effect size (a 50 % relative risk reduction).

**Table 2 Tab2:** Sample size assuming 5 % level of significance, 90 % power, 50 % relative risk reduction

Incidence of primary outcome in ‘no decision-support’ group	Incidence of primary outcome in ‘decision-support’ group	Relative risk	Total sample size required
3 per 1000	1.5 per 1000	0.5	46,000
4 per 1000	2 per 1000	0.5	34,000
5 per 1000	2.5 per 1000	0.5	27,000
6 per 1000	3 per 1000	0.5	22,000

#### Primary analysis

The primary analysis will be a comparison of women and babies allocated to “CTG with no decision support” with “CTG with decision support”. Participants will be analysed in the groups into which they were randomly allocated, regardless of allocation received. All women and babies with available data will be included, except for protocol violations and women randomised in error who did not give consent or who were under 16 years of age. The number (percentage) of babies with the composite primary outcome will be presented for each group, and the risk ratio plus 95 % confidence interval (CI) will be calculated. Risk ratios will be estimated using generalised estimating equations (GEE), or a similar method, adjusting for the stratification factors used in the randomisation (centre and singleton/twin pregnancy). This method of analysis will account for the correlation in outcomes between twins and siblings delivered in a subsequent pregnancy during the trial period. A log binomial model will be used in the first instance, but if convergence is not achieved then a log Poisson model will be used with a robust variance estimator [40]. The mean (SD) PARCA-R Composite score will be presented for each group, and the mean difference between groups plus 95 % CI will be calculated and compared using GEE (Gaussian model with identity link). For secondary outcomes including the components of the primary outcome, a 1 % level of statistical significance will be employed. Both adjusted and unadjusted estimates will be presented for all outcomes, but the primary inference will be based on the adjusted analysis.

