### Planned interventions

The intervention is the decision-support software in this trial. In order to accurately reflect any potential impact of the decision-support software in contemporary NHS practice, such as changes in midwifery presence during labour consequent upon knowledge of the allocation, it is desirable that clinicians are not masked to allocation.

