### Review of primary outcome

During the early part of the trial, and with advice from the DMC, the primary outcome definition was refined to ensure it captured babies who were likely to have experienced hypoxia during labour. The component of the primary outcome “*Admission to neonatal unit within 48 h of birth for ≥ 48 h with evidence of feeding difficulties, respiratory illness or encephalopathy (where there is evidence of compromise at birth)*” was initially capturing a range of conditions, many of which were unlikely to be related to hypoxia. As a consequence, a process of reviewing each case which fulfilled this component of the primary outcome was implemented. Neonatal unit discharge summaries are collected for all babies admitted to the neonatal unit within 48 h of birth for more than 48 h. For the purposes of data monitoring during the trial, two members of the co-investigator group reviewed all cases which fulfilled this criteria and using a defined data extraction form, ascribed each case as meeting the primary outcome or not. The data extraction form included key elements of the neonatal course which are most likely to be related to intrapartum hypoxia. The form is not an established or validated list of criteria and the numeric scoring was devised to give some quantification of the severity of elements of the clinical course. A score of 3 or greater was agreed to be evidence that the condition of the baby was likely to be associated with intrapartum hypoxia, acknowledging that there remained uncertainty about this, as there is no absolute measure of intrapartum hypoxia. For the final analysis, all cases meeting the broad primary outcome criteria will be reviewed by an independent panel of neonatologists to repeat this process of ascribing each case (masked to allocation) as fulfilling the definition fo the primary outcome or not. Each case will be reviewed (independently) by at least 2 neonatologists and disagreements will be resolved by discussion by the group of five neonatologists.

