#### Economic evaluation

All analyses will be conducted on the basis of intention-to-treat. As the data for costs are likely to be skewed, we shall use non-parametric bootstrap estimation to derive 95 % confidence intervals for mean cost-differences between the trial groups [41]. Non-parametric bootstrap methods will also be used to calculate 95 % confidence intervals for incremental cost-effectiveness ratios. In the absence of stochastic data for all variables, a series of multi-way sensitivity analyses will be undertaken, to explore the implications of uncertainty on the base-case incremental cost-effectiveness ratios. In addition, cost-effectiveness acceptability curves will be constructed using the net-benefits approach [42].

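### The primary analysis excludes protocol violations as an undefined category of its own, which conflicts with the as-allocated rule beside it and permits exclusions after randomisation that may depend on arm

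*Protocol article*

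**What the plan says.** Two consecutive sentences of the protocol article's Primary analysis section define who is analysed. The first is an as-allocated rule: "Participants will be analysed in the groups into which they were randomly allocated, regardless of allocation received". The second sets the exclusions: "All women and babies with available data will be included, except for protocol violations and women randomised in error who did not give consent", and it goes on to add women under 16.

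Three other statements bear on the point:

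- Planned interventions, on care: "it is desirable that clinicians are not masked to allocation".
- Review of primary outcome, on the final panel of neonatologists: the panel's task is "ascribing each case (masked to allocation) as fulfilling the definition" of the primary outcome.
- Economic evaluation: "All analyses will be conducted on the basis of intention-to-treat".

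**The concern.** The exclusions for absent consent and for age under 16 are defensible, because both facts are fixed before allocation. Protocol violations are a different matter. The sentence joins them to the women randomised in error as a further category, and nothing in it restricts them to facts that predate allocation.

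In this trial the only difference between the arms is whether the decision-support software runs. Running it for a woman allocated to none, or not running it for a woman allocated to it, is naturally a protocol violation. The first sentence keeps such a woman in her allocated group, while the second can remove her.

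If exclusions follow events after randomisation, and if those events or their detection differ by arm, the comparison is no longer protected by randomisation. Two features add to the exposure. Clinicians are unmasked. Also, under Quality of care, the notes of babies with an adverse outcome are reviewed with the allocation left visible, so violations could plausibly be noticed more often among event cases, although the article does not say so. The primary outcome is expected in only 3 per 1000 controls, so each event case carries weight.

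**Working it through.** **Step 1. Side by side.** Take a woman allocated to decision support whose software did not run.

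- As-allocated sentence: analysed in the decision-support group.
- Exclusion sentence: removable, if this counts as a protocol violation.
- Economic evaluation: included, under intention-to-treat.

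The masked panel does not resolve this. It decides whether a baby meets the outcome, not whether a woman enters the analysis.

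**Step 2. Reproduce the design.** The Effect size section gives 23,000 women per arm and "a 50 % reduction in poor neonatal outcome rate from 3 to 1.5 per 1000", "assuming a 5 % level of significance and 90 % power". Sidedness is not stated for this outcome; two-sided is assumed. With p1 = 0.003, p2 = 0.0015 and mean p = 0.00225:

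- n per arm = [1.96·√(2p(1−p)) + 1.2816·√(p1(1−p1) + p2(1−p2))]² / (p1−p2)² = 0.21719² / 0.0015² ≈ 20,966, a total of 41,932.
- With continuity correction: n' = (n/4)·[1 + √(1 + 4/(n(p1−p2)))]² ≈ 22,279, a total of 44,558.

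The stated 46,000 is a little above the corrected figure. At 23,000 per arm the power is about 91% with the correction and 92.4% without it, so the stated 90% is met.

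Expected events: 23,000 × 0.003 = 69 control and 23,000 × 0.0015 = 34.5 intervention.

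**Step 3. How many event cases must be dropped from one arm to change significance?** Pooled two-proportion test: z = (a/n1 − b/n2) / √[p(1−p)(1/n1 + 1/n2)], with p = (a+b)/(n1+n2). Dropped cases leave both numerator and denominator.

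| Control v intervention events | p, all included | Dropped | p after |
|---|---|---|---|
| 69 v 34 (planned effect) | 0.0006 | 17 control | 0.052 |
| 69 v 35 (planned effect) | 0.0008 | 16 control | 0.054 |
| 69 v 69 (no difference) | 1.00 | 22 intervention | 0.041 |
| 69 v 44 | 0.019 | 5 control | 0.054 |
| 69 v 47 | 0.041 | 2 control | 0.061 |
| 69 v 49 | 0.065 | 2 intervention | 0.041 |
| 69 v 50 | 0.081 | 3 intervention | 0.041 |
| 69 v 52 | 0.122 | 5 intervention | 0.041 |

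A change caused by 2 to 5 cases therefore needs a full result roughly between p = 0.02 and p = 0.12.

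**Step 4. Long-run error rates.** Simulation of 400,000 binomial trials, 23,000 per arm, same test, two-sided 5%:

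- Null, 3 per 1000 in both arms: type I error is 5.0% with nobody dropped, 7.7% with 5 intervention events dropped and 15.6% with 10.
- Planned effect: power is 93% with nobody dropped, 85% with 5 control events dropped and 71% with 10.

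**Step 5. Exclusions unrelated to outcome.** Dropping 1% of women (460 in all, 230 per arm) removes 230 × 0.003 ≈ 0.7 events from an arm at the control rate. This is negligible.

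These calculations ignore the planned adjustment for centre and plurality and the clustering of twins and siblings, which matter little here.

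**The case against.** The strongest reply is that the two sentences can be read together. The as-allocated rule already keeps women who received the wrong arm, and the remaining items in the exclusion list are entry errors, so protocol violations may mean entry errors too. The Guardian system asks its eligibility questions before it allocates, so such errors could be judged on facts that predate randomisation. That reading is possible, but the text lists violations separately and does not say it. If it is what was meant, removing the words costs nothing.

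A second reply is that the definition of a violation, and who judges it, are commonly left to the analysis plan, which is not shown. That is right, and no missing definition is counted here. The exclusion itself, however, is stated in the article and attached to the primary analysis.

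Several stronger inferences should be resisted:

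- A reader might infer that two excluded babies would reverse the trial. That needs both to be event cases, both in one arm, and a result already beside the 5% boundary; any trial there is that fragile.
- A reader might infer that staff who know the allocation will pick the violations. The article says only that clinicians giving care are unmasked, not who identifies violations or when.
- A reader might infer that costs and effects will certainly come from different women. The authors may regard their analysis set as intention-to-treat, so the sets may differ but need not.
- A reader might infer that any bias would be irrecoverable. Labour data and outcomes for all participants are held on Guardian and sent centrally, so a re-analysis that includes the excluded women would be possible.

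**Conclusion.** The point holds as a conflict in the stated rule. Followed literally, the clause permits post-randomisation exclusions from the primary analysis, possibly dependent on arm, next to a sentence that promises the opposite. It does not show that the analysis will depart from the as-allocated comparison, because the narrow reading remains open.

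The size of any bias is unknown, since the article gives no number of violations. The effect ranges from negligible, for exclusions unrelated to outcome, to material when event cases are lost from one arm: at 5 cases, type I error of 7.7% instead of 5.0%, or power of 85% instead of 93%. A result as strong as the one planned would survive unless 16 to 17 control events were dropped. These figures assume two-sided 5% testing, 23,000 per arm, the planned event rates and an unadjusted comparison.

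**What to change.** Delete the words *protocol violations and* from the exclusion sentence, so that the primary analysis leaves out only women randomised without consent or aged under 16, and report those exclusions by arm. State that the economic evaluation uses the same set. Confine any analysis without other protocol violations to a labelled sensitivity analysis, with violations judged masked to both allocation and outcome.

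Settle this before anyone sees outcome data by allocation. The main change is to one sentence, with short additions for the economic evaluation and the sensitivity analysis. The sample size stays at 46,000 and no new data are needed.

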### Trial eligibility and randomization

Women admitted to a participating labour ward who fulfil all of the following criteria will be eligible to be randomised if:they are judged to require continuous electronic fetal monitoring (EFM) by the local clinical team based on their existing guidelines, and the woman consents to have EFM, and EFM is possible*Note: continuous EFM is defined as the active decision of the health care professional and the woman to initiate continuous EFM for the purpose of fetal monitoring, usually because of a perceived risk factor(s) which increases the likelihood of fetal compromise occurring in labour. The Guardian system will prompt the health care professional to consider women eligible for the INFANT trial if the CTG is used.**The decision to initiate continuous EFM can occur at any time during labour. Some women with known factors which place them at higher risk of fetal compromise during labour will already know that continuous fetal monitoring throughout labour is planned. Others will start off labour with intermittent monitoring and then be judged to require continuous fetal monitoring at some point during the labour. There is no point during labour at which women are not eligible to participate (this includes during the second stage).*they have a singleton or twin pregnancythey are ≥ 35 weeks’ gestation (≥245 days)there is no known gross fetal abnormality, including any known fetal heart arrhythmia such as heart blockthey are 16 years of age or olderthey are able to give consent to participate in the trial as judged by the attending clinicians.

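### The adjusted PARCA-R model names no prognostic covariate beyond the randomisation strata, although gestation is known at entry; adding it would be a small, nearly free gain in precision.

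*Protocol article*

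**What the plan says.** The Primary analysis section of the Protocol article gives the PARCA-R composite one sentence on modelling: the mean difference and its interval "will be calculated and compared using GEE (Gaussian model with identity link"). That sentence lists no covariates.

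Adjustment factors are named once, in the earlier sentence on risk ratios for the short-term composite: "adjusting for the stratification factors used in the randomisation (centre and singleton/twin pregnancy"). The section ends with a rule covering every outcome: "Both adjusted and unadjusted estimates will be presented for all outcomes, but the primary inference will be based on the adjusted analysis". Read together, these make centre and plurality the only covariates the article defines for the PARCA-R estimate that carries the inference.

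Two other places bear on what could be added. Trial eligibility and randomization requires "≥ 35 weeks’ gestation (≥245 days"), so gestation must be known before allocation. The Pre-specified subgroup analysis section lists suspected growth restriction at the start of labour.

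On size, the Effect size section states that "we can estimate a mean (SD) 2 year score of 96 (SD33"), and that "a follow up sample of size 7000 (3500 per arm) in the INFANT study would have over 90 % power" for a 3-point difference, tested two-sided at 5%.

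**The concern.** PARCA-R is one of the trial's two primary outcomes. The note under Long term says it is measured to give reassurance that any short-term benefit was not bought with later developmental delay. For that purpose the reader looks chiefly at the width of the interval around the mean difference.

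In a linear model, variance in the outcome that a baseline variable could explain, but that is left unexplained, goes into the standard error. A covariate fixed before randomisation can remove part of it. This leaves the target of estimation unchanged and, with thousands of children, costs almost nothing in degrees of freedom.

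The two strata were chosen to balance the randomisation, not to predict development. The Effect size section expects fewer than 1% of births to be twins, so plurality can explain very little. The same section treats maturity as related to the score: it places term infants half a standard deviation above a preterm sample. That makes gestation a reasonable candidate that the plan does not use.

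**Working it through.** **Inputs from the article.** SD 33, 3500 children per arm, difference 3 points, two-sided 5% (all Effect size).

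**Assumed input.** R², the share of variance explained by the added covariates beyond the strata. The article gives no value, so 2%, 5% and 10% are shown as a range.

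**Step 1: reproduce the stated power.**
- SE = 33 × √(2/3500) = 0.789.
- Power = Φ(3/0.789 − 1.96) = Φ(1.84) = 96.7%, which agrees with the claim of over 90%.
- 95% half-width = 1.96 × 0.789 = 1.55 points.
- Difference detectable with 90% power = 0.789 × (1.960 + 1.282) = 2.56 points.

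**Step 2: add covariates.** The residual SD becomes 33 × √(1 − R²), and SE and half-width shrink by the factor √(1 − R²). The equivalent number of extra children is 7000/(1 − R²) − 7000.

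| R² (assumed) | SE | Half-width | Narrower by | Power | Equivalent extra children |
|---|---|---|---|---|---|
| 0 | 0.789 | 1.546 | – | 96.7% | – |
| 2% | 0.781 | 1.531 | 1.0% | 97.0% | 143 |
| 5% | 0.769 | 1.507 | 2.5% | 97.4% | 368 |
| 10% | 0.748 | 1.467 | 5.1% | 98.0% | 778 |

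A simulation of 7000 children in 24 centres (number assumed), with one covariate at R² = 10%, compared a strata-only fit with one that added the covariate. The SE fell from 0.790 to 0.749, or 5.2%, against 5.1% from the formula. Narrowing the interval by more than 10% needs R² of about 20% (10.6%).

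**Step 3: fewer questionnaires returned.** The article gives no return rate. Assuming 60%, there are 2100 per arm:
- R² = 0: half-width 2.00, power 83.8%.
- R² = 2%: 1.98, 84.5%.
- R² = 5%: 1.95, 85.6%.
- R² = 10%: 1.89, 87.4%.

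The proportional narrowing is the same as in step 2. The gain in power is larger because power starts lower.

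**Step 4: cost of missing covariate values.** If a complete-case fit loses a fraction m of the children, the SE is multiplied by √((1 − R²)/(1 − m)). This equals 1 when m = R². At R² = 2%, losing 2% of the children cancels the whole gain.

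**The case against.** The case against is substantial, and most of it stands.

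- **The restriction is inferred.** The PARCA-R sentence names no covariates at all. Strata-only adjustment follows from the risk-ratio sentence and the closing rule for all outcomes. A longer list could sit in a statistical analysis plan that is not shown. This stands as a caution, but the article does say which estimate carries the inference and defines only one adjustment set for it.
- **The gain is small.** At the planned size the half-width falls by 0.015 to 0.08 points on a score with SD 33, and power is already 96.7%. This stands.
- **Predictor strength is undocumented.** The half-SD contrast compares preterm with term infants, while eligibility starts at 35 weeks, so gestation within the trial may explain little. This stands; it is why R² is given only as an assumed range.
- **Availability is partial.** Infant sex is not listed as collected. Data collection warns that centres do not all record the same fields, so growth restriction may be missing for some children. The eligibility rule gives a threshold in days but does not say how gestation is stored. This narrows the candidate list but leaves gestation in place.
- **Age at questionnaire completion is not a baseline variable.** It arises about two years after allocation in a trial where clinicians are unmasked. This stands, and it belongs outside the main model.

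A reader might infer more: that strata-only adjustment biases the PARCA-R comparison, that it leaves the follow-up underpowered, or that the trial already holds a full set of strong predictors. The article supports none of these. Randomisation protects the estimate, the stated power reproduces with room to spare at full return, and only gestation is clearly known for every woman.

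**Conclusion.** The point holds as a minor refinement. The planned PARCA-R analysis is valid, and the article contains no mistake here. It does pass over a baseline variable known for every participant in a model where one more term costs almost nothing.

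Over an assumed R² of 2% to 10%, the interval would be 1.0% to 5.1% narrower, and power at 3500 per arm would rise by 0.3 to 1.3 percentage points. The benefit in power becomes more noticeable only if returns fall well short of 7000; at the assumed 60% it is 0.7 to 3.6 points. If gestation from 35 weeks onward explains less than 2% of the variance, the gain is negligible, though still harmless. The conclusion rests on reading the stratification factors as the whole adjustment set for PARCA-R, which an unseen analysis plan could change.

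**What to change.** Before outcome data are examined by allocated group, specify the following for the adjusted PARCA-R model:

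- Add gestational age at trial entry, besides centre and plurality, after confirming that it is stored as a value.
- Add infant sex and suspected growth restriction only if they are held. State a rule, such as a missing category, so that no child is dropped for an absent covariate.
- Report the unadjusted estimate, as already planned, and a strata-only estimate as sensitivity analyses.
- Use age at questionnaire completion only in a further sensitivity analysis.
- Keep labour and birth-condition variables out of the model, since they arise after randomisation.

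The cost is a few lines in the analysis plan and a few model terms. Gestation needs no new data collection, and the sample size is unaffected.
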